# **Design and rationale of the Healthy 4U-2 trial of a telephone based intervention of a blend of motivational interviewing and cognitive behaviour treatment for physical activity behaviour change and maintenance: a randomised controlled trial protocol.**

## **BACKGROUND**

Non communicable diseases (NCDs) are the leading cause of illness, disability and death in Australia, accounting for 90% of all deaths in 2011 [1]. NCDs have an intricate association with modifiable risk factors such as physical inactivity, poor nutrition, and smoking [2]. Hospitals, as a result, have been required to broaden their role from their primary focus of disease treatment towards a position of more integrated health promotion and holistic care [5].

Hospitals are in a suitable position within the health care system to be advocates for health promotion [6]. Hospitals represent the primary concentration of health resources, professional skills and medical technology in the [5]. Moreover, hospital-based clinicians are seen as credible sources of advice and expertise on health issues that extend beyond their responsibilities for services related to sick care [7]. The extensive resources that hospitals command mean that even a small shift of focus has the potential to bring about an increase in resources dedicated to health promotion [5,6]. This shift, over time, could bring potential health benefits to a community [5, 7]. The hospital healthcare system also provides important opportunities to reach the most disadvantaged in the community, who are often hard to reach by wider population-based approaches [8].

Surgeons working in the hospital system have an important role in the promotion of healthy lifestyles and behaviour change for patients with, or at risk of, chronic disease [9]. Due to their extensive training, specialisation and medical expertise, surgeons are perceived as dependable

sources of advice and expertise on health issues that extend beyond their responsibilities for services related surgical care [6]. Surgeons as such, are influential in the promotion of lifestyle behaviour change [7]. Hospital surgeons also have significant influence over clinical settings, and by extension, institutional policy and practice [10]. The surgical profession is one of responsibility and leadership, playing key roles in strategic planning, especially pertaining to clinical care [10].

Patients have stated that they would like, and to some extent expect the healthcare system to provide some guidance on lifestyle behaviour change and physical activity (PA) [12]. Doctors practicing in hospitals have stated that they do not have sufficient time to spend with patients giving advice on preventive measures [13]. The working intensity of doctors make it difficult to spend sufficient time with patients discussing preventive health [13]. Unpublished data from Bendigo Health supports this, with doctors indicating that discussions about smoking, nutrition and physical activity (SNAP) health risk factors are very important for health, yet, at the same time they are not a high priority. This has resulted in low implementation rates of preventative health practices.

The H4U study demonstrated that integrated motivational interviewing (MI) and cognitive behaviour therapy (CBT) resulted in significant changes in physical activity and health related outcomes for secondary care participants. The H4U-2 extends the H4U study in a number of ways including: (i) increased focus of the intervention on maintenance of behaviour change; (ii) a longer follow-up timeframe to test the maintenance effect of the intervention; decrease in intervention number from 8 sessions to 5; and (iii) referrals by surgeons into the program. The H4U-2 offers surgeons a pathway to integrate preventive health into clinical care, delivering a brief intervention to at risk patients, and referring the patient in an efficient manner to a dedicated resource.

The primary objective of this study is to determine the effectiveness of lifestyle intervention in secondary care patients presenting to a non-admitted elective clinic in a public hospital who do not participate in enough physical activity to be deemed sufficiently physically active. Secondary aims relate to the effect of the MI/CBT intervention on self-efficacy, quality of life, and anthropometric measures. In addition, this study will investigate the acceptability, feasibility cost-effectiveness of delivering the telephone intervention in this setting.

## **METHODS AND ANALYSIS**

### **Design**

The H4U-2 project is a randomised controlled trial with assessment of outcomes at three points- baseline, post 12 weeks and 9 months designed and reported in line with the CONSORT recommendations for reporting (Figure 1). The study will be conducted at large regional tertiary public hospital that's serves a wide geographical region, with a socioeconomically diverse population. A total of 136 patients who present to BH Specialist Clinic as an elective admission will be recruited and included in the project (figure 1). The trial will be registered with the Australian and New Zealand Clinical Trials Registry prior to patient recruitment. The study will commence 01/12/18 and commence 01/12/22.

### **Randomisation**

Participants who fulfil the inclusion criteria and consent to take part in the trial will randomised to either the intervention or the control group based on a random number sequence produced by a computer generated program (randomizer.org). Assignments will be prepared and sealed in sequentially numbered opaque envelopes. Assignment will be made by opening the next envelope in the sequence, after the recruiter determines eligibility for the study, participants

consent to take part, and baseline measurements are completed.

[figure not shown]

Figure 1: CONSORT Flow Chart

## Study population

### *Group 1*

The project target population is patients presenting to the BH Specialist Outpatients Clinic over a 12 month recruiting period. These patients are elective non-emergency presentations for a consultant with a medical specialist. Patients will be eligible if they are fluent in conversational English and insufficiently physically active (not participating thirty minutes or more of moderate

physical activity on at least five days a week- 150 mins/week) [10]. The exclusion criteria are: under 18 years and over 69 years; poor comprehension of English language (determined by project team); too physically active (participating in more than thirty minutes of moderate physical activity on at least five days a week); deaf/hearing impaired; disabling neurological disorder; severe mental illness such as psychosis, learning disability, dementia and cognitive impairment; registered blind; housebound or resident in nursing home; unable to move about independently or not ambulatory; pregnancy; advanced cancer. For those people who are ineligible or decline to participate, we will keep a 'screening log' of basic demographic information and reasons for non-participation.

*Group 2 Participants as medical record audits.*

A comparison cohort of patients attending Specialist Clinics will be selected for audit of healthcare usage over the study period. The Group 2 participants will be drawn from the Specialist Clinic client management records by Specialist Clinic administration staff. All the data will be retained in a study location on the password protected Bendigo Health corporate drives. The data collection timeframe is 1 September 2018 to 1 Dec, 2020.

## **Recruitment**

All participants will be recruited from the BH Specialist Outpatients Clinic following the same pathway (figure 1):

- During the recruitment time-frame participating consultants will be provided with sequentially numbered invitational fliers to be distributed to potential participants. The fliers invite patients to participate in the project (appendix 1). The information flier will briefly detail to the patients what the project will entail and the exclusion criteria. This

pathway is an important step in the project design- clinicians who have a relationship with the individual may be in a good position to highlight the project, and its potential significance to the individual. This referral pathway is has the potential to be more sustainable in the long term aim of integrating health promotion into existing practice.

- A project team member will speak to all potential participants and provide details of the project. Potentially interested participants will be given the Patient Information Sheet and Consent (PICF)- the PICF form gives an in-depth synopsis of the project (appendix 2). A project team member will go through the project details and the PICF with any interested person. Potentially interested participants will also be given a copy of the PAR-Q which needs to be completed as part of inclusion criteria.
- To limit pressure and coercion on the individual, the PICF does not need to be signed and completed at that time. The participant may take the PICF home to read and discuss with others. Completed PICF's will be collected at the briefing sessions. Participants will be given a stamped addressed envelope which they can return the PICF to the project team should they wish.
- Participants who express an interest in participation but want to take time to consider their choice will be offered a follow-up phone call from the project team to further discuss the project. A project team member will take the participants phone number and discuss appropriate times to contact them.
- Follow-up calls to potential participants will follow the same structure:
  - A member of the project team will make all follow-up calls.
  - Potential participants will be contacted on the number that they supply to the project team.
  - Potential participants will be informed that they will be contacted no sooner than one week after talking to the project team member. This time will allow the individual time to consider their decision.
  - Should the project team member call and the individual does not answer, no message will be left. The project team member will make two attempts to contact on this occasion. If no contact is made no message will be left on this occasion.

136 In this circumstance the project team member will try to contact the individual  
137 again, a minimum of four days later. Two calls will be attempted, with a voice  
138 message left should the second attempt be unsuccessful. The message left will  
139 be scripted for uniformity:

140 *“Hello [potential participant], this is [project team member] from Bendigo Health*  
141 *calling you in regards to the Health 4U project that we discussed with you in the*  
142 *specialist outpatient clinic. This call is following up on our conversation about*  
143 *your potential interest in participating in the project. If you would like to discuss*  
144 *this further please contact the Healthy 4U team directly on [name]. Thank*  
145 *you”.*

- 146 ○ After leaving a voice message one more attempt at contact will be made, a  
147 minimum of four days later. If this call is unsuccessful no message will be left at  
148 this time, and no further contact will be attempted.
- 149 ○ If, on speaking to a potential participant the individual states that they are no  
150 longer interested in participating in the project the project officer will thank the  
151 individual for their time and consideration, and inform the individual that no  
152 further contact will be instigated by the project team.
- 153 ○ If, on speaking to a potential participant the individual states that they are still  
154 unsure about whether they are interested in participating in the project the project  
155 officer will ask if the individual would like to be contacted again to follow this up.  
156 Subsequent calls will follow the structure as above.
- 157 ○ For individuals who choose to participate in the project, a project team member  
158 will book them into one of the mandatory briefing sessions. A number of sessions  
159 will be held to accommodate participant schedules, including day and evening  
160 sessions. During this phone call the project team member will:
  - 161 ▪ Remind participants to bring their PICF to the briefing session.
  - 162 ▪ Discuss availability of briefing session times and dates, and book the  
163 participant into the most suitable session.

- 164                                   ▪ Check that the potential participant has completed a PAR-Q and that they  
165                                   bring it to the briefing session.
  
- 166                   • At the briefing session participants will complete their outcome measures (appendix 4).  
167                   Completion of the outcome measures should take approximately fifteen minutes.  
168                   Members of the project team can assist during this time. The outcome measures will be  
169                   taken prior to any briefing interventions. Participants will be informed that repeat  
170                   measures are required after week 12 and at 9 months.
  
- 171                   • At the end of the briefing session, the participants will be allocated into their respective  
172                   groups- group 1 or group 2. This allocation will be completed through a computer-  
173                   generated program. The particulars of each group will be outlined below in this  
174                   document.
  
- 175                   • All participants will be asked to attend two follow-up sessions, one after the 12-week  
176                   intervention and the other at 9 months. A number of sessions will be held to  
177                   accommodate participant schedules, including day and evening sessions. During  
178                   attendance at the sessions repeat outcome measures will be taken and accelerometers  
179                   will be fitted again. As a direct consequence of the social distancing measures resulting  
180                   from the Covid-19 pandemic, no group measurements will be undertaken from 31 March  
181                   2020. For the remaining participants, self-reported measures of mass and waist-  
182                   circumference will be recorded. Accelerometers will be delivered to participants, and  
183                   collected at a designated time in a sealed envelope with no individual contact required.  
184                   In situations where participants reside in geographic locations that prohibit delivery,  
185                   accelerometers will be posted to participants, with a stamped envelope to return the  
186                   accelerometers. All accelerometers and bands will be cleaned in line with  
187                   recommendations from the Department of Health and Human Services.
  
- 188                   • All participants will be offered a survey to complete as part of process evaluation  
189                   (appendix 5). This survey will be distributed at the follow-up session and can also be  
190                   completed online via survey monkey, and/or mail out copies.
  
- 191                   • Participants who withdraw from the study who wish that their data is not included in the  
192                   analysis will be required to complete a withdrawal of consent form.

193

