### 265 **Study Outcomes**

The primary endpoint is a change in physical activity levels, measured at 3 points- baseline, 13-weeks, and at 9 months (Table 1). Secondary endpoints include a change in self-efficacy, quality of life, waist circumference, BMI, and smoking status (Table 1.)

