**Table 1. Primary and secondary outcome measures**

| Primary and secondary outcome measures                                                                                                                                                                                                                                                                                              |
|-------------------------------------------------------------------------------------------------------------------------------------------------------------------------------------------------------------------------------------------------------------------------------------------------------------------------------------|
| Primary 

Physical Activity – ActiGraph [43]

                                                                                                                                                                                                                                          |
| Secondary 

Self-Efficacy- Modified physical activity self-efficacy survey [44]

Quality of Life: SF-12 Survey [49]

Waist Circumference- within AUSDRISK tool [50]

Smoking- within AUSDRISK tool [50]

Nutrition- within AUSDRISK tool [50]

BMI

 |

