**Sample Size and Statistical Analysis**

To compare differences in our outcome measures a series of 3 x 2 mixed model ANOVAs will be undertaken. Utilizing data from the H4U study, to detect an effect size of 0.35 or greater, with the alpha set at .05, and the power set at .90, a sample size of 50 participants per arm will be required. Protecting against a drop-out rate of 20% over the 9 month period, 68 participants will be recruited and randomized into each arm. The study therefore aims to recruit approximately 136 participants.

A full intention-to-treat principle will be used. For participants with missing data at 3 month and 9 month the last-observation-carried forward approach will be adopted (Shao and Zhong, 2003). Repeat sensitivity analyses will be undertaken to provide indication that the imputed values have a significant effect on the outcome.

313

314 **Process measures**

315 The project team will log the number of referrals made by the surgeons in Specialist Clinic. The  
316 project team will record patient feedback regarding interest and opinions on the project, which is  
317 hoped may give insight into future program development strategies.

318 A log will be maintained of how many project participants contact the project team during the  
319 intervention phase, the reason for contact, the method of contact and the outcome. During any  
320 non-structured contact no intervention is to be delivered at that time.

321 To examine the acceptability of the H4U study, participants allocated to the intervention group  
322 will also be administered an additional questionnaire, after the 9 months follow up. This  
323 questionnaire will include items addressing satisfaction with the components of the project, their  
324 perceived utility of the intervention. The questionnaire will also address whether participants  
325 attended a community health program, and the frequency of visits. To obtain a more in-depth  
326 understanding of the potential barriers and facilitators at the service delivery and individual level  
327 to uptake of this programme, we will also conduct semi structured interviews with a subsample  
328 of participants in the intervention group. Recruitment for the interviews will be purposive to  
329 maximise variation such as urban/rural location, gender and age for patients. Sampling will  
330 continue until no new themes or categories emerge from the data (the so-called thematic  

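### BMI and waist change from session measurement to self-report on 31 March 2020 but are still analysed as one repeated measure, so 9-month change mixes true change with a change of method

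*Protocol*

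**What the plan says.** At baseline, the Recruitment section says: "At the briefing session participants will complete their outcome measures (appendix 4"). Project staff may help. At follow-up, participants come to sessions after week 12 and at 9 months, and during "attendance at the sessions repeat outcome measures will be taken and accelerometers" fitted again. The same bullet then gives the pandemic change: "no group measurements will be undertaken from 31 March" 2020, and those still in follow-up supply "self-reported measures of mass and waist" circumference. Accelerometers continue by delivery or post.

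Study Outcomes keeps both measures as change endpoints: "Secondary endpoints include a change in self-efficacy, quality of life, waist circumference, BMI, and smoking status". Table 1 lists one source for waist, "Waist Circumference- within AUSDRISK tool [50"], and no second mode.

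Sample Size and Statistical Analysis treats all outcomes alike: "To compare differences in our outcome measures a series of 3 x 2 mixed model ANOVAs will be undertaken". Missing 3- and 9-month values are filled by last-observation-carried-forward, and the only sensitivity analyses named concern those imputed values.

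**The concern.** The method of obtaining mass and waist changes part-way through the trial, but the endpoint and its analysis do not. A participant with a session-based baseline and a self-reported 9-month value has a change score that contains the difference between two methods.

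The timing makes this matter. The longer follow-up was added to test maintenance, and on the stated dates the change of method falls on the 9-month visit alone. If people tend to under-report mass or waist, the trial would show late loss in both arms. If participants coached by telephone under-report more than controls, the excess would look like a maintained treatment effect. Participants cannot be unaware of their arm: one arm receives five calls and the other no further routine contact beyond a reminder.

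**Working it through.** The protocol gives no figure for this point, so there is none to reproduce. The check is date arithmetic followed by a simple bias formula.

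**Inputs from the protocol**
- Start date 01/12/18 (Design).
- 12-month recruiting period (Study population).
- Follow-up after week 12 and at 9 months (Recruitment); week 13 in Study Outcomes.
- Switch date 31 March 2020 (Recruitment).
- 136 participants (Sample Size and Statistical Analysis).

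**Assumption:** uniform accrual from 01/12/18 to 01/12/19. Drop-out is ignored.

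**Share of visits after the switch**
- 9 months (274 days): affected if randomised after 1 July 2019. Share = 153/365 = 0.419, and 0.419 × 136 = 57. By whole months, 5/12 = 0.417.
- Week 13 (91 days): affected only if randomised after 31 December 2019, which is after recruitment closes. Share = 0.
- If 9 months is counted from the end of the 12-week intervention (358 days): affected if randomised after 8 April 2019. Share = 237/365 = 0.649, and 0.649 × 136 = 88.

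Slower recruitment would raise the 9-month share and could reach the week-13 visit. Anyone enrolled after the switch would, however, be self-reporting throughout and have no within-person change of method.

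**Effect on within-arm change**

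Shift in the 9-month mean = share × mean self-report error. An average under-report of 1 kg (assumption) gives 0.42 × 1 = 0.42 kg of apparent loss in each arm.

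**Effect on the arm comparison**

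Bias = share × (error in intervention arm − error in control arm). The protocol gives no size for this difference, so the inputs are assumptions (kg or cm):

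| Differential error | Bias at share 0.42 |
|---|---|
| 0 | 0 |
| 0.5 | 0.21 |
| 1 | 0.42 |
| 2 | 0.84 |

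At an assumed height of 1.70 m, 0.84 kg is 0.84/1.70² = 0.29 kg/m² of BMI.

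**Cost of using session-measured values only**

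With 1 − 0.417 = 0.583 of 9-month values left, the standard error ratio is √(1/0.583) = 1.31. This assumes the late values are left missing.

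**What carry-forward would do instead**

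Under the protocol's missing-data rule, the excluded values would be replaced by week-13 values. The 9-month contrast would become 0.583 × (9-month effect) + 0.417 × (week-13 effect). If a 2 kg effect at week 13 had faded to zero (illustration), the analysis would still show 0.417 × 2 = 0.83 kg as maintained.

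**The case against.** The strongest reply is that the switch follows a calendar date and applies to both arms of a randomised trial. Error common to both arms cancels from the arm contrast in expectation. This stands. A reader might infer that the 9-month arm comparison is necessarily biased, but the documents do not support that. Bias needs differential reporting, which is plausible but nowhere quantified, and zero is a legitimate lower bound. Common error still distorts within-arm change and the time effect.

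A reader might also infer that staff measured everyone before the switch. The protocol does not say so. Participants complete their measures at the session, staff may assist, and waist sits within the AUSDRISK tool. Session-based measurement follows from the contrast with self-report, but who held the tape is not stated, so the size of the method change is unknown.

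It can also be said that mode terms and sensitivity sets belong in a statistical analysis plan, which is not shown. That is fair for the detail. But this protocol itself fixes both the change of method and the single analysis.

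Finally, simply setting late values to missing would trigger carry-forward and could do as much harm as the problem. That is correct, and discarding those data from the main comparison is a debatable trade. The restricted analysis should therefore stand beside the planned one and be exempt from carry-forward.

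**Conclusion.** The point holds in a limited form. Followed as written, the plan gives a mixed-mode 9-month change for BMI and waist. About 42% of 9-month values (about 57 of 136) and no week-13 values would be self-reported, given the stated dates and uniform accrual; the share is about 65% if 9 months runs from the end of the intervention. Within-arm change and the time effect are affected by any systematic difference between the methods. The arm comparison is affected by about 0.42 times any differential error, from zero upwards.

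Collecting self-reported values was a reasonable response to social distancing and is not criticised; pooling them unmarked is. Only two secondary endpoints are involved. The change should be made, but the trial's main conclusion does not depend on it.

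**What to change.** - Record the mode, session-measured or self-reported, with every mass and waist value.
- Alongside the planned analysis, prespecify a BMI and waist analysis restricted to session-measured values. Fit it with a likelihood-based mixed model and state that last-observation-carried-forward does not apply to it.
- Report the all-values analysis with a mode term and an arm-by-mode term. Mode coincides with the pandemic period, so these terms cannot separate method from period; say so when reporting.
- Do not claim maintained BMI or waist change if it appears only in self-reported values.

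The cost is one data field and some analysis wording. The restricted analysis is less precise at 9 months, with a standard error about 1.3 times larger under the accrual assumption, before any gain from modelling the earlier visits.
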